### Exclusion criteria

Patients are excluded if they have other types of diabetes than T2D, are at risk stratification level 1 or 3 (Table 1), are pregnant or breastfeeding, have severe co-morbidity with a life expectancy less than 5 years, or are under such conditions that they will not be able to attend or complete the appointments (e.g. due to dementia or psychiatric conditions). Furthermore, we will exclude patients who are either participating in other studies that potentially may affect the primary outcome of our study, or patients participating in studies which include blood sampling amounting to > 5 % of the blood volume in a 2 month period prior to the randomisation and/or the follow-up visits. The risk stratification level is assessed by the endocrinologist during the 12- and 24-months follow-up. If the patient has shifted from level 2 to level 3, the patient is excluded from the study. These patients will be offered long-term follow-up in the diabetes outpatient clinic. Patients changing from level 2 to level 1 will continue their participation in the study.

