### Inclusion criteria

Patients with T2D over the age of 18 years, able to understand, speak and write Danish, willing to give oral and written consent, and at predefined risk stratification level 2, are eligible for the study. According to the risk stratification model applied (Table 1), patients with T2D can be stratified into three levels: level 1 (uncomplicated), level 2 (intermediate risk) or level 3 (high risk). The model is an organisational tool intended to graduate the medical care and treatment according to the severity and complexity of T2D. Patients stratified at level 1 have well-controlled T2D and are recommended to be followed in general practice, whereas patients at level 3 are recommended to be followed in hospital-based outpatient clinics, as they have dysregulated T2D and/or increasing severity of complications and/or co-morbidity. Patients stratified at level 2 are moderately dysregulated T2D and/or having incipient complications. These patients are recommended to be followed in closer collaboration between hospital and general practice. The model was originally defined in a report from the Capital Region of Denmark compiled by diabetes specialists, other experts and GPs [26] and based on current evidence on treatment goals and cut-off points in diabetes management [27–30]. In the present trial, the model is slightly modified to make the model more operational. In a recent study of the population in our outpatient clinic, we found that 54 % of the patients were stratified to level 2, while less than 5 % were stratified to level 1 [31].

**Table 1 Tab1:** Risk stratification model for patients with type 2 diabetes

	Level 1	Level 2	Level 3
HbA_1c_ (mmol/mol)	<53	53–75	>75
Blood pressure, systolic/diastolic (mm Hg)	<130/80	130/80–160/90	>160/90
Metabolic complications	No	Severe insulin resistance^a^	Very fluctuating plasma glucose^b^ or severe hypoglycaemia
CVD^d^	No	One previous MACE	>1 MACE, symptomatic CVD or NYHA II-IV
Diabetic foot disease	No	Peripheral neuropathy^c^ or artery disease^d^	Previous or existing ulcer or Charcot foot
Retinopathy	No or simplex retinopathy	Progression of retinopathy	Macula oedema or proliferative retinopathy
Nephropathy	No	Micro-albuminuria^e^	Macro-albuminuria^f^

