All parameters in level 1 have to be fulfilled to be allocated to risk stratification level 1. At risk stratification level 2, at least one parameter has to be fulfilled in level 2, and none in level 3. Patients at level 3 have to fulfil at least one of the parameters in level 3 [16].

*HbA*
_*1c*_ haemoglobin A_1c_, *CVD* cardiovascular disease, *MACE* major cardiovascular event, *NYHA* the New York Heart Association functional classification in patients with heart disease [36]

^a^Severe insulin resistance: Insulin dose > 2.0 U/kg/day

^b^Very fluctuating plasma glucose: Daily plasma glucose values of > 15 mmol/L or < 5 mmol/L

^c^Peripheral neuropathy: Vibration perception threshold ≥ 25 mV evaluated by a biothesiometer

^d^Peripheral artery disease: Ankle-brachial index < 0.9 with or without symptomatic claudication

^e^Micro-albuminuria: > 1 occasion of urine albumin/creatinine ratio between 30 and 299 mg/g

^f^Macro-albuminuria: Urine albumin/creatinine ratio ≥ 300 mg/g or an estimated glomerular filtration rate < 45 mL/min

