### Study data

All study data will be collected in connection with the annual comprehensive check-up in the outpatient clinic at the baseline-screening visit, as well as 12, 24 and 36 months after baseline. Data will be obtained from medical records, laboratory databases, self-reported patient questionnaires and face-to-face by the primary investigator who does not take part in the treatment or care of the patients. All data will be registered in an Epidata database [32]. The database is stored at Gentofte Hospital in a secure purpose-designed password-protected web-based file system.

The primary outcome is the difference in mean HbA_1c_ between the two groups measured at 12-, 24- and 36-months follow-up. The secondary outcome is the proportion of patients who meet the set of Danish standard indicators reflecting quality of care at 12, 24 and 36 months follow-up [33]. These indicators cover seven areas, including HbA_1c_, blood pressure, low density lipoprotein, albuminuria, fundus photography, foot examination, smoking status and proper treatment and control of these factors. The indicators are primarily based on process variables, but do include a few numerical variables.

Other outcomes are listed below:

*Clinical characteristics:* Blood pressure, weight and body mass index.

*Diabetes-related laboratory parameters and characteristics:* C-peptide, insulin, lipids, liver function tests, kidney function tests, electrolytes, coagulation factors, thyroid-stimulating hormone, cardiovascular biomarkers, vitamin D, urine albumin/creatinine ratio, and registration of diabetes-related medication.

*Healthcare professionals’ experiences with shared care:* A questionnaire evaluating the experiences of the participating GPs and the endocrinologists after the completion of the 12- and 36-month follow-up periods.

*Patient-reported outcomes:* Estimation of general quality of life, diabetes-related symptoms, alcohol consumption patterns as well as patients’ experiences of family network and function.

The four questionnaires used are:

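### Randomised patients who worsen to level 3 leave the study while those who improve stay; if shared care is truly worse, the 24- and 36-month HbA1c comparisons are biased towards non-inferiority

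*Protocol article*

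**What the plan says.** All references are to the protocol article.

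- **When level is re-assessed (Exclusion criteria).** "The risk stratification level is assessed by the endocrinologist during the 12- and 24-months follow-up".
- **Patients who worsen (Exclusion criteria).** "If the patient has shifted from level 2 to level 3, the patient is excluded from the study". Their care is then described: "These patients will be offered long-term follow-up in the diabetes outpatient clinic". No study measurement after removal is described.
- **Patients who improve (Exclusion criteria).** "Patients changing from level 2 to level 1 will continue their participation in the study".
- **What makes a patient level 3 (Inclusion criteria, Table 1 and its note).** One criterion is enough: "Patients at level 3 have to fulfil at least one of the parameters in level 3". The HbA1c row gives the cut-offs for levels 1, 2 and 3 as "HbA_1c_ (mmol/mol) <53 53–75 >75". Other level 3 entries include blood pressure above 160/90, more than one MACE, foot ulcer, macula oedema, macro-albuminuria and severe hypoglycaemia.
- **Primary outcome (Study data).** The difference in mean HbA1c "between the two groups measured at 12-, 24- and 36-months follow-up".
- **Where data are collected (Study data).** "All study data will be collected in connection with the annual comprehensive check-up in the outpatient clinic".
- **Test and size (Statistical analysis; Population size calculation).** Non-inferiority by a two-sided 90% confidence interval, margin 4.4 mmol/mol, SD 10, power 0.8, 10% dropout, 140 patients, sized on HbA1c at 12 months.

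**The concern.** The rule acts after randomisation, and one of its triggers is a high value of the primary outcome itself. It cuts off the upper tail of HbA1c and leaves the lower tail untouched. If shared care controls HbA1c less well, more of its patients cross 75 and leave. The patients who remain in the two arms then look more alike than the randomised groups would.

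In a superiority trial such shrinkage would usually be conservative. In a non-inferiority trial it favours the claim under test. The 24- and 36-month comparisons both follow a removal step, and both belong to the stated primary outcome.

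Several other level 3 triggers are harms that a trial of moving care out of a specialist clinic would want to count. Once a patient is out of the study, later events of that kind are not observed.

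**Working it through.** **1. Reproduce the planned size.** Per arm n = 2 × (1.645 + 0.842)² × 10² / 4.4² = 63.9, so 64 per arm and 128 in total. With 10% dropout this is 128/0.9 = 143, or 128 × 1.1 = 141. The stated 140 therefore agrees with a one-sided 5% test and a true difference of zero. After 10% dropout, 140 × 0.9 / 2 = 63 per arm, which is used below.

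**2. Show the mechanism by hand.** For HbA1c ~ N(μ, 10), the mean of those at or below 75 is μ − 10 × φ(b)/Φ(b), with b = (75 − μ)/10.
- Control, μ = 60: b = 1.50, 6.7% removed, mean of the rest 60 − 1.39 = 58.61.
- Shared care, μ = 64.4: b = 1.06, 14.5% removed, mean of the rest 64.4 − 2.66 = 61.74.
- The difference falls from 4.4 to 3.13.

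This shows the direction but overstates the size. It discards the values at the removal visit itself, and it ignores that only level 2 patients enter, so baseline HbA1c is at most 75.

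**3. Model the visits as the article sets them out.** Four visits (0, 12, 24 and 36 months) are simulated with SD 10, equal correlation between visits, baseline capped at 75, and shared care worse by 4.4 from 12 months on. Patients above 75 at 12 months have no 24- or 36-month value; those above 75 at 24 months have no 36-month value. Non-inferiority is claimed when the 90% limit on the unfavourable side (shared care minus control) lies below 4.4.

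The SD and margin come from the article. The control mean, the correlation and the true difference are assumptions, because the article does not give them. Only the HbA1c trigger is applied.

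Removed, at control mean 60 and correlation 0.5–0.7: about 4–5% of control and 11–12% of shared-care patients at 12 months; 7–9% and 17–20% cumulatively by 24 months.

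| Comparison | Expected difference, control mean 60 | False non-inferiority, control mean 60 | Expected difference, control means 58–64 | False non-inferiority, control means 58–64 |
|---|---|---|---|---|
| 12 months, all values kept | 4.4 | 5% | 4.4 | 5% |
| 24 months | 3.7–3.9 | 9–11% | 3.5–3.9 | 8–14% |
| 36 months | 3.3–3.6 | 12–15% | 3.0–3.7 | 11–20% |
| 12 months, only if removed patients' values are dropped | 3.3 | 17–18% | 2.8–3.5 | 14–27% |

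Ranges cover correlation 0.5–0.7. Simulation error on the rates is a few tenths of a percentage point.

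**4. Equal arms.** With a true difference of zero, removal is the same in both arms and the simulated difference stays within about 0.03 of zero at every visit.

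**The case against.** **The powered comparison may be intact.** Level is assessed at the check-up where HbA1c is measured, so the 12-month value exists when removal is decided, and nothing says it is thrown away. If it is kept, the 12-month difference stays at 4.4 and the error at 5%. This stands. A reader might infer that the comparison on which 140 rests is biased; the text supports that only under the added assumption that the value is dropped.

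**The bias is conditional.** With equal arms it is about nil. This also stands, but the truly-worse case is the one a non-inferiority test has to guard against.

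**The other level 3 criteria.** A reader might suppose that they all add to the bias. The documents do not support that. Removal for blood pressure, eye, foot or kidney findings shifts mean HbA1c only as far as those findings are related to HbA1c, and for severe hypoglycaemia the direction is unclear.

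**How often patients will move to level 3.** The Inclusion criteria section reports 54% of the clinic's patients at level 2 and under 5% at level 1, which leaves more than 41% at level 3. It is tempting to conclude that transitions will be frequent. That figure is a cross-sectional share in a hospital clinic where level 3 patients are recommended to be followed, and it is not a progression rate. The trial also recruits patients managed solely by their GP.

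**An analysis plan not shown may define the analysis set.** It may, but the point is an explicit rule and not an omission. An analysis set cannot restore 24- and 36-month values that were never collected.

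**Conclusion.** The concern holds for the 24- and 36-month HbA1c comparisons. The rule removes patients after randomisation, partly on the primary outcome, and in one direction only. If shared care is truly worse by the margin, the risk of a false claim rises from 5% to about 8–14% at 24 months and 11–20% at 36 months, under the assumptions listed in the working.

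For 12 months the article leaves the matter open: no effect if removed patients' values are kept, about 14–27% if they are dropped. It does not support saying that the 12-month comparison is biased as it stands, or that shared care will be found non-inferior because of the rule. The size depends on an assumed control mean, correlation and true difference; the direction, when shared care is worse, does not change across the range tried.

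**What to change.** Leave the clinical hand-over of level 3 patients exactly as written, and separate it from study participation. Replace the consequence in "If the patient has shifted from level 2 to level 3, the patient is excluded from the study" with wording to this effect: *the patient remains in the study; HbA1c and the other outcomes are still collected at the 12-, 24- and 36-month check-ups in the outpatient clinic; all patients are analysed in the arm to which they were randomised.* State also that the 12-month value of a patient who reaches level 3 at that visit is retained. Add progression to level 3, by arm, as a pre-specified outcome.

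The cost is a short amendment and continued annual measurement. These patients are already offered follow-up in the clinic where study data are collected. Recruitment began in August 2015, so the first 12-month assessments fall around August 2016, after the article's publication in June 2016.

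There is one real drawback. Shared-care patients who move to clinic follow-up receive care in the control setting, which may itself draw the arms together at 24 and 36 months. An analysis of those who stayed in their programme does not guard against this, because that set is truncated in the same way. The as-randomised result should therefore be read together with progression to level 3 by arm.

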### Randomisation

Patients will be randomised to the intervention or control groups in a 1:1 ratio. The randomisation sequence is computer generated by a statistician, who is not participating in the study. A secretary in the outpatient clinic will handle the script and instructions. The secretary will prepare sealed envelopes in accordance with instructions, and the envelopes will be stored and administered by the secretary during the period of inclusion. There will be an envelope prepared for each GP, and we will randomise the patients in blocks of two since we aim at each GP having an equal number of patients in the intervention and control group. The randomisation will be performed immediately after the baseline screening visit. Healthcare professionals involved in the study, including the principal investigator, will be blinded to the randomisation process. The allocation will be revealed after the screening visit. Further blinding is not possible due to the circumstances of the intervention.

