### Participants

We will recruit eligible patients followed for T2D by either their GP or at the outpatient clinic. A patient is only eligible if their GP accepts participation in the study. Therefore, we will recruit GPs before recruiting study participants. Invitations to participate will be distributed by mail to all regional GPs referring patients to Gentofte Hospital. We intend to include approximately 25 GPs, aiming at recruiting six patients from each practice or until we have reached the predefined number of patients in the study (n = 140). An endocrinologist and the primary investigator will make appointments for visiting GPs who have accepted to participate. The duration of the individual visit at the GP’s office will be of approximately 2 hours. During the visit, we will identify patients who are eligible to participate according to the inclusion criteria. Patients managed by the GP and patients previously referred from the individual GP to be managed at the outpatient clinic are identified. Thus, both patients who have their T2D managed solely by their GP, or at the outpatient clinic, will be recruited. Eligible patients will be contacted by phone and, if the patient shows interest in participating in the study, written information will be sent by regular mail or e-mail. If the patient agrees to participate in the study by giving written consent, she/he will be invited to a baseline-screening visit in the outpatient clinic (Fig. 2). If all inclusion criteria are fulfilled and none of the exclusion criteria are met, patients will then be randomised to one of the two groups. Patients who decline to participate or do not meet the inclusion criteria will continue their usual T2D care either at the GP or at the outpatient clinic.

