### Population size calculation

A power calculation was conducted according to criteria for non-inferiority trials [42, 43], and based on the primary outcome measure Hb_A1c_ at 12-month follow-up. The non-inferiority margin was set at 0.4 % (1 % is approximately 11 mmol/mol) based on both clinical judgement and a guideline from the European Medicines Agency identifying the non-inferiority margin for HbA_1c_ above 0.3 % (3 mmol/mol) [44]. The standard deviation of HbA_1c_ was set at 10 mmol/mol, based on a recent study on patients with risk stratification level 2 attending our outpatient clinic [31]. With a non-inferiority margin at HbA_1c_ 4.4 mmol/mol, an alpha of 0.05 and a power at 0.8, as well as an estimated dropout rate of 10 %, the sample size has been estimated to 140 participants.

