### Statistical analysis

We will present and compare the baseline demographics as well as clinical and diabetes-related characteristics of the intervention and the control group. The statistical comparison will be conducted on the basis of *t* tests or analysis of variance as appropriate for comparing means and χ^2^ tests for categorical or binary data. The primary outcome will be tested by constructing a 90 % two-sided confidence interval for the difference of the means of HbA_1c_ between the intervention and the control group. We use the lower bound to determine non-inferiority. Other outcomes will be tested with superiority analyses such as linear or logistic regression analysis. For observed differences we will consider a *P* value less than 0.05 as statistically significant.

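### GP is the randomisation stratum and, in the shared-care arm only, the main care provider, yet the stated primary interval has no GP term; the effect is modest and its direction is not fixed

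*Protocol article*

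**What the plan says.** Patients are randomised individually, 1:1. On how this is organised, the Randomisation section says: "There will be an envelope prepared for each GP". Allocation is in blocks of two, with the aim of equal arm sizes within each GP. The Participants section gives the scale: "We intend to include approximately 25 GPs, aiming at recruiting six patients from each practice", up to a total of 140.

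The Intervention group section places one yearly visit at the outpatient clinic and three at the patient's own practice, which otherwise works in its customary way. The settings and Control group sections keep control patients entirely at the clinic.

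The Statistical analysis section says that the primary outcome is tested by "constructing a 90 % two-sided confidence interval for the difference of the means of HbA_1c_ between the intervention and the control group". Regression is mentioned only for the other outcomes. The Population size calculation is "based on the primary outcome measure Hb_A1c_ at 12-month follow-up". It states "The standard deviation of HbA_1c_ was set at 10 mmol/mol" and uses "an alpha of 0.05 and a power at 0.8", with a margin of 4.4 mmol/mol and 10% dropout. Neither section mentions GP, a stratum or an ICC.

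**The concern.** GP plays two parts in this design, and each affects the standard error in a different direction.

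- **GP as stratum.** Differences between practices that are common to both arms cancel from the treatment difference, because the arms are balanced within GP. A simple two-sample standard error still counts them, so the interval is too wide and the precision gained by blocking is lost.
- **GP as provider in one arm.** If practices differ in how well they run shared care, outcomes are correlated within GP in that arm only. A simple standard error leaves this out, so the interval is too narrow. The Discussion itself expects the GPs to vary in their interest in and knowledge of diabetes.

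The second effect matters more, because it makes a false claim of non-inferiority more likely. The trial's conclusion is read from a single confidence bound. If the handling of GP is not fixed beforehand, a borderline bound leaves a choice between two defensible intervals after the data are seen.

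**Working it through.** **Inputs from the article.** Margin 4.4 mmol/mol, SD 10, one-sided alpha 0.05 (implied by the 90% two-sided interval), power 0.80, dropout 10%, N = 140, about 25 GPs with six patients each (three per arm). **Assumed, because the article gives no value:** ICC 0.05 to 0.10.

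**Reproducing the plan's figure.** n per arm = 2 × 10² × (1.645 + 0.842)² / 4.4² = 63.9, so 64 per arm and 128 in total. Allowing for dropout gives 128/0.9 = 143, or 128 × 1.1 = 141. Both are close to 140. One-sided 0.025 would give 183. The planning formula is therefore the independent-sample one, with no GP component.

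**Base case.** 140 × 0.9 = 126 evaluable, 63 per arm. SE = 10 × √(2/63) = 1.78. The 90% half-width is 1.645 × 1.78 = 2.93 mmol/mol. Power = Φ(4.4/1.78 − 1.645) = 79.5%.

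**Effect of GP.** Let V be the true variance of the difference divided by the simple variance. The actual one-sided error of the simple interval is 1 − Φ(1.645/√V).

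- Common to both arms: V = 1 − ICC.
- Shared-care arm only, m = 3 per GP: V = [(1 + (m − 1)ICC) + 1]/2 = 1 + ICC.
- Both present, ICC 0.05 each: V = [0.05 + 0.90/3 + 0.95/3]/(2/3) = 1.00.

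| GP effect | ICC | √V | Correct half-width | Error of simple interval |
|---|---|---|---|---|
| Common | 0.05 | 0.975 | 2.86 | 4.6% |
| Common | 0.10 | 0.949 | 2.78 | 4.2% |
| Shared-care arm only | 0.05 | 1.025 | 3.00 | 5.4% |
| Shared-care arm only | 0.10 | 1.049 | 3.07 | 5.8% |
| Both | 0.05 + 0.05 | 1.00 | 2.93 | 5.0% |

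With clustering in the shared-care arm only, power with the correct SE is 77.8% (ICC 0.05) or 76.1% (ICC 0.10), and the required total is 150 or 157 against 143.

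**Simulation.** 60,000 trials, 21 GPs with three patients per arm each, SD 10, true difference at the margin. The simple interval had one-sided error of 4.5% and 4.3% (common ICC 0.05, 0.10), 5.4% and 5.7% (shared-care arm only), and about 5.0% with both. This agrees with the formulas.

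**Which GP model.** In the same simulations, a common GP term alone gave 5.5 to 6.1% error whenever the GP effect differed by arm. It removes the conservative component and leaves the anti-conservative one in place. An analysis that allows for GP-by-arm variation held about 5%. Its power was about 74 to 75% with clustering in the shared-care arm only, where the simple interval has about 78 to 79%.

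**Baseline HbA1c.** With baseline-to-follow-up correlation r, power = Φ(4.4/(1.78√(1 − r²)) − 1.645). The article gives no r. Assuming 0.3 gives 83% and 0.6 gives 93%, before any GP-by-arm term.

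**The case against.** The strongest reply is that the article is a condensed text and the SAP is not shown. The Statistical analysis section names an interval for a difference of means but no variance estimator. It does not say that patients are treated as independent or that the stratum is ignored, and the t tests it mentions follow the sentence on baseline comparisons. This stands in part: a reader might infer that the analysis is declared unstratified, and the text does not say so. What the article does fix is a primary interval described without GP, regression reserved for other outcomes, and a sample size that matches independence.

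A second reply is that the two mechanisms pull in opposite directions, that no ICC is given, and that they can cancel exactly. This stands in full. A reader might conclude that the interval's width is wrong; the documents establish neither the sign nor the size of any error.

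A third is that patients, not practices, are randomised, so the usual cluster-trial inflation of both arms does not apply. This also stands. It does not remove clustering that arises through delivery in one arm.

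Finally, an obvious repair, a random GP intercept common to both arms, can make the error worse. That is correct, and it determines the form of the fix.

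**Conclusion.** The point holds as a low-severity mismatch. The stated primary analysis and the sample size do not reflect that GP is both the randomisation stratum and the main provider of care in one arm. For assumed ICCs of 0.05 to 0.10 and about three patients per arm per GP, the standard error changes by about −5% to +5%, and the simple interval's one-sided error lies between about 4.2% and 5.8% by formula. Only clustering in the shared-care arm works towards a false non-inferiority claim. The figures rest on assumed ICCs, equal numbers per GP and normal outcomes. The documents do not support the stronger statement that the trial is materially underpowered or its interval invalid.

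**What to change.** State that the primary 90% interval comes from a model of 12-month HbA1c on arm and baseline HbA1c that accounts for GP and includes, in the primary model, a GP-level random effect specific to the shared-care arm (GP-by-arm). With some 25 GPs, use small-sample degrees of freedom. Analysing within-GP arm differences is equivalent in a balanced design. A common GP intercept alone should not be primary, and the arm-specific term should not be left to a sensitivity analysis.

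The cost is wording: envelopes are prepared by GP, so GP identity is known, and HbA1c is collected at baseline. The statistical price is a few points of power for the GP-by-arm term. Baseline adjustment is likely to offset it, but the net figure depends on a correlation that the article does not give. The planned 140 need not change for this point alone.

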### Trial status

The trial is ongoing. The recruitment of patients started August 2015 and is expected to be completed by December 2016.

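### Fixed blocks of two within each GP let anyone who knows the block size deduce up to about half of the allocations before the patient is screened

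*Protocol article*

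**What the plan says.** All points are from the protocol article.

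- **Ratio and blocks (Randomisation).** "Patients will be randomised to the intervention or control groups in a 1:1 ratio". Blocking is within practice, so that the arms stay level there: "we will randomise the patients in blocks of two since we aim at each GP having an equal number of patients". One block size is given, with no variation. The envelopes are likewise organised by practice: "There will be an envelope prepared for each GP".
- **Timing and blinding (Randomisation).** "The randomisation will be performed immediately after the baseline screening visit". Then: "The allocation will be revealed after the screening visit. Further blinding is not possible due to the circumstances of the intervention".
- **Safeguards (Randomisation).** A statistician outside the study generates the sequence, a clinic secretary prepares and holds sealed envelopes, and the health professionals and principal investigator are said to be kept unaware of how randomisation is run.
- **Recruitment (Participants).** About 25 GPs, "aiming at recruiting six patients from each practice", to a total of 140. Candidates are identified at a visit to the GP. Contact by phone, written consent and the eligibility decision at the screening visit all come before randomisation.
- **Calendar (Trial status).** "The recruitment of patients started August 2015 and is expected to be completed by December 2016". The article is dated 4 June 2016.

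**The concern.** In a block of two, the first allocation fixes the second. Because the blocks are formed within each GP and allocations are open once revealed, anyone who knows the block size and has seen a GP's first allocation knows the second, and likewise the fourth and the sixth. The envelopes then conceal only the first member of each pair.

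This matters because several steps come before randomisation: who is contacted next, how participation is presented, and how a borderline patient is classified. If the next arm is known, these steps can depend on it, consciously or not. The groups may then differ at baseline in ways that chance does not explain and that measured covariates may not capture. In a non-inferiority trial with a margin of 4.4 mmol/mol, a modest imbalance could move the estimate towards or away from the margin.

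**Working it through.** **The plan's own figure.** Inputs from Population size calculation: SD 10, margin 4.4 mmol/mol, power 0.8, dropout 10%. A one-sided alpha of 0.05 follows from the 90% two-sided interval in Statistical analysis.

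- Per arm: 2 × [10 × (1.645 + 0.842) / 4.4]² = 63.9, so 64 per arm and 128 in total.
- With dropout: 128 / 0.9 gives 143, and 128 × 1.1 gives 141.

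The stated 140 is reproduced to within about 2%. It serves as the base below and is not itself in question.

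**Allocations certain in advance under blocks of two.** A GP with m patients has floor(m/2) determined allocations.

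- Six per GP: 3 of 6, so 70 of 140 (50%).
- 140 patients from exactly 25 GPs, as 15 with six and 10 with five (90 + 50): 15 × 3 + 10 × 2 = 65 of 140 (46%).
- Five in every GP: 28 × 2 = 56 of 140 (40%).
- Parallel screening: if a share s of second members is screened before the first is revealed, 70 × (1 − s) remain known. The article does not give s. For assumed values of 0, 0.25 and 0.5, the result is 70, 52.5 and 35.

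A best guess is right for half of first members and all second members: (0.5 + 1) / 2 = 75%, against 50% under full concealment.

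**Alternatives, at six patients per GP.**

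- *Fixed block of size 2h.* Certain share = 1/(h + 1). Correct-guess rate = [h + (2^(2h)/C(2h,h) − 1)/2]/(2h). For h = 1 these give 50% and 75%. For h = 3 they give 25% (35 of 140) and [3 + (64/20 − 1)/2]/6 = 68%.
- *Random mix of 4 and 6, equally likely, current size unknown.* An allocation is certain only when the history shows that a block of six is in use and one arm is used up. Three alike at the start has probability ½ × 2/20 = 0.05 and fixes three positions. One arm reaching three at the fourth position has probability ½ × 6/20 = 0.15 and fixes two. The expected number is 3 × 0.05 + 2 × 0.15 = 0.45 of 6, or 7.5% (10.5 of 140). Enumeration of all sequences gives a best-guess rate of 67%.
- *One balanced batch after all of a GP's patients are screened.* No allocation is predictable before screening.

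**Power of an analysis of first members only.** Power = Φ(4.4 / [10√(2/n)] − 1.645), with n per arm.

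- 70 patients (n = 35): Φ(1.841 − 1.645) = 58%.
- 63 patients after 10% dropout (n = 31.5): Φ(1.746 − 1.645) = 54%.

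**What selection could do (assumed shifts).** Suppose selection moved the mean of the predictable half by d in opposite directions in the two arms. Each arm mean would move by d/2, and the unadjusted difference by d. For d = 0.5, 1 and 2 mmol/mol this is 11%, 23% and 45% of the margin, with either sign.

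**The case against.** The strongest reply is that deducible does not mean known, and known does not mean acted upon.

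- **Knowledge of the block size.** Staff are said to be kept unaware of the randomisation procedure, and before publication that may have covered the block size. This stands for the earlier period. It gives no protection to anyone who has read the article.
- **Half is a ceiling.** It needs even counts per GP and strictly sequential screening. This stands, and the range above reflects it.
- **Limited discretion.** Risk level 2 (Table 1) rests mostly on numeric cut-offs, and candidates are identified at the GP visit, probably before that GP's first allocation. This largely stands. What remains exposed is the order of contact, consent and a few items that need judgement, such as ability to attend, life expectancy and symptomatic cardiovascular disease.
- **Purpose.** Blocks of two keep the arms level when a GP recruits only a few patients. Any larger block gives up some of that.

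A reader might infer that the endocrinologist and the primary investigator choose, phone and screen the patients themselves while knowing the arm. The Participants section does not support this: it places these two at the GP visit but does not say who phones or who decides eligibility at screening. A reader might also infer that easier patients would be steered to shared care and so hide inferiority. Nothing in the article indicates a direction. It does plan to compare baseline characteristics by arm, which could show gross selection on measured factors but not selection on unmeasured ones.

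**Conclusion.** The point holds as a weakness of the design. A single fixed block of two within each GP, with allocations revealed one at a time and no later blinding, makes up to about half of the allocations deducible before screening: 70 of 140 at six per GP, 65 of 140 with 25 GPs, and fewer with parallel screening. This assumes that someone involved in contact, consent or eligibility knows the block size and the GP's earlier allocations. The first is easy once the article is published, with recruitment planned to run on to December 2016.

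The article does not support saying that concealment has failed for half of the sample, or that the result is biased. It shows that the design permits selection, in an unknown direction, and that the stated blinding of staff does not prevent it. The block size is fixed in the protocol itself, so this is not a detail left to an analysis plan. The severity is moderate: the weakness is real and cheap to reduce for the GPs still to come.

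**What to change.** For GPs not yet opened, do one of the following:

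1. Have the external statistician issue a new sequence with randomly varying block sizes, for example 4 and 6, that are disclosed neither to staff nor in print. Certainty in advance falls from 50% to about 7.5%. The best-guess rate falls less, from 75% to 67%.
2. Screen all of a GP's patients first and then randomise them as one balanced batch. Nothing is predictable before screening, and the balance within the GP is kept.

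A fixed block of six is not advisable. It matches the planned number per GP, so it is easily inferred and leaves 25% of allocations certain.

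The cost is new envelopes and a short amendment. Option 1 can leave an imbalance of up to three patients in a GP that stops early. Option 2 delays randomisation and requires a change to the rule that it follows each screening visit at once.

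Neither option helps patients already allocated. At publication about 10 of the 17 recruitment months (August 2015 to December 2016) had passed. The report should therefore state how many patients were allocated under blocks of two. An analysis of the first patient of each pair, whose allocation could not be deduced, can be added as a supportive check only, with its power of about 54–58% stated beside the planned 80%.
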